### Ancillary and post-trial care {34}

Ancillary and post-trial care is not needed for the current research study.

### Outcomes {16}

Demographic data such as age, gender, BMI, and duration of knee pain will be collected. The number and type of co-morbid illnesses will be recorded.

All outcome measures will be assessed at baseline, 16, 32, and 52 weeks. The primary outcome will be the Western Ontario and McMaster Universities Osteoarthritis Index (WOMAC; 5-point Likert) pain at 52 weeks. WOMAC is well-known to be the “gold standard” self-reported measure in KOA trials [19, 41]; a validated Chinese version of the WOMAC, with good internal consistency (Cronbach’s alpha > 0.7) and test–retest reliability (intraclass correlation coefficients > 0.80), will be used in this study [42].

Secondary outcomes include a set of biopsychosocial parameters: Physical function will be measured subjectively by WOMAC function subscale [42] and objectively by the 30-second chair and stand performance test [42, 43]. Lower limbs muscle mass will be measured by bioimpedance analysis [44]. Physical activity level will be measured by the Chinese International Physical Activity Questionnaire (Short form) [45]. Self-management efficacy will be measured by Pain-Self Efficacy questionnaire [46]. Generalized Anxiety Disorder-7 (GAD-7) and Patient Health Questionnaire-9 (PHQ-9) will be used to measure anxiety and depression, respectively [47, 48]. Insomnia will be measured by the 7-item Insomnia Severity Ind ex (ISI) [49], and loneliness will be measured by the 6-item De Jong Gierveld Loneliness Scale [50, 51]. EuroQuol-5D-5L (EQ-5D-5L) questionnaire will be used to measure health-related quality of life [51].

Other outcomes, including analgesics prescriptions, can be accurately recorded in the electronic medical records, but their consumption, along with over-the-counter drugs, will be logged using medication logs. To maintain a comprehensive record, patients will be provided with medication diaries to note down details such as the name, dosage, frequency, and any specific instructions for each analgesic they take. During regular assessment timepoints, patients will be asked to complete questionnaires that utilize the Timeline Followback method to inquire about their medication usage in the past 14 days. This method involves presenting patients with a calendar and having them retrospectively recall their intake of analgesics over a 14-day period [20].

Cost-effectiveness: cost-effectiveness will be analyzed if the intervention is effective in reducing WOMAC pain score. Quality-adjusted life years (QALYs) of the participants will be assessed by EQ-5D-5L, which is also one of our outcomes. The EQ-5D-5L health state classification instrument has five dimensions: mobility, self-care, usual activities, pain/discomfort, and anxiety/depression. Each dimension has five levels to indicate the severity of the problem in that dimension. The Hong Kong reference value sets will be used to covert EQ-5D-5L health status to the utility weight. Individuals’ QALY will be calculated by using the area under the curve approach. Self-reported data on health service utilization in the past three months will be collected at 0 months and 12 months; this will include hospitalization (frequency and days), visits to GOPCs, specialist out-patient clinics (SOPCs), and the emergency departments. The information on health service use in the public health system will be supplemented by records in the Hospital Authority electronic medical system. The cost of this program such as costs directly related to setup, administration, clinical management, and exercise courses will be recorded. But additional costs related to evaluation and research will not be included.

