### Sample size {19}

There will be two arms in the study: (i) the intervention group (RAMP-Knee OA); and (ii) the control group (usual care). The sample size will be calculated based on the suggested minimal important clinical difference (MCID) of the WOMAC pain score, which is 0.469 in terms of standardized mean difference between groups [52]. Thus, a sample size of 97 in each arm will have 90% power to detect an effect size of 0.469 in a two-sample *t*-test with alpha set at 0.05 (G* power 3.1.9.7). Assuming a 15% dropout rate, the total sample size is 228, with 114 in each arm.

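### The cost-effectiveness analysis depends on an undefined pain result, so the joint cost and QALY result may be withheld when it is still informative

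*Protocol article*

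**What the plan says.** Under Outcomes {16} the protocol states that "cost-effectiveness will be analyzed if the intervention is effective in reducing WOMAC pain score". The sentence recurs word for word under Plans for assessment and collection of outcomes {25a}. It says *if* rather than *only if*, but no section gives another route to the analysis. *Effective* is not defined: it could mean statistical significance, reaching the minimal important difference, or a favourable direction.

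The economic outcome is not pain: "Quality-adjusted life years (QALYs) of the participants will be assessed by EQ-5D-5L, which is also one of our outcomes", and "Individuals’ QALY will be calculated by using the area under the curve approach". All outcome measures, EQ-5D-5L included, are taken at baseline and at 16, 32 and 52 weeks. The cost inputs are also collected without any condition: "Self-reported data on health service utilization in the past three months will be collected at 0 months and 12 months", and "The cost of this program such as costs directly related to setup, administration, clinical management, and exercise courses will be recorded".

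The endpoint behind the condition is a single time point: "The primary outcome will be the Western Ontario and McMaster Universities Osteoarthritis Index (WOMAC; 5-point Likert) pain at 52 weeks".

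**The concern.** The condition and the analysis that it controls concern different quantities, in three ways.

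- **Outcome.** Of the five EQ-5D-5L dimensions that the protocol lists, pain/discomfort is one. The others are mobility, self-care, usual activities and anxiety/depression. The programme includes exercise and psychosocial counselling, and Objectives {10} hypothesises gains in function, psychosocial health and quality of life. QALYs could therefore differ between arms without a demonstrated pain effect.
- **Time.** An area under the curve counts benefit at 16 and 32 weeks. A benefit that has faded by week 52 still contributes QALYs but can fail the condition.
- **Cost.** Differences in hospital stays, clinic visits and emergency visits bear on cost-effectiveness whatever happens to pain.

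Two consequences follow. The joint cost and QALY result may never be produced although its inputs were collected. If it is produced, it comes from the subset of possible trials in which a correlated outcome turned out well, which pushes the QALY difference upward. Because *effective* is undefined, whether the analysis runs could also be decided after the pain result is seen.

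**Working it through.** **1. The plan's own figure.** Sample size {19} gives the target effect, "which is 0.469 in terms of standardized mean difference between groups", and states that "a sample size of 97 in each arm will have 90% power to detect an effect size of 0.469" with alpha 0.05. The exact two-sided two-sample t-test has power 0.9015 at 97 per arm and 0.898 at 96, so 97 reproduces. Allowing for 15% dropout, 114 × 0.85 = 96.9. The steps below use 97 per arm.

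**2. Assumptions that the protocol does not supply.**
- *Effective* means two-sided p<0.05 in favour of RAMP-Knee OA (z > 1.96).
- True pain effect d: 0.469 (design), 0.35, or 0.235 (about half the design value).
- Correlation ρ between the estimated pain and QALY differences: 0.3 to 0.7.

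**3. Formulas, in SD units.**
- SE = √(2/97) = 0.1436 (unadjusted).
- m = d/SE.
- P(run) = 1 − Φ(1.96 − m); P(withheld) = 1 − P(run).
- Mean excess of the pain estimate when the analysis is run: b = SE × φ(1.96 − m)/P(run).
- Upward shift of the standardised QALY difference: ρ × b, taking the same SE for both outcomes.

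Worked case, d = 0.469: m = 0.469/0.1436 = 3.266 and 1.96 − m = −1.306, so P(run) = 0.904. With φ = 0.170, b = 0.1436 × 0.170/0.904 = 0.027. The QALY shift is 0.3 × 0.027 = 0.008 to 0.7 × 0.027 = 0.019.

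**4. Results with the unadjusted SE.**

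| True pain effect | Run | Withheld | Mean pain estimate when run | QALY shift, ρ 0.3–0.7 |
|---|---|---|---|---|
| 0.469 | 90% | 10% | 0.496 (×1.06) | 0.008–0.019 SD |
| 0.35 | 68% | 32% | 0.425 (×1.21) | 0.022–0.052 SD |
| 0.235 | 37% | 63% | 0.381 (×1.62) | 0.044–0.102 SD |

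**5. With ANCOVA.** Statistical methods {27a} plans baseline-adjusted ANCOVA. With an assumed baseline correlation of 0.5, SE = 0.1436 × √(1 − 0.25) = 0.1244.

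| True pain effect | Run | Withheld | QALY shift, ρ 0.3–0.7 |
|---|---|---|---|
| 0.469 | 96% | 4% | 0.003–0.007 SD |
| 0.35 | 80% | 20% | 0.013–0.030 SD |
| 0.235 | 47% | 53% | 0.031–0.073 SD |

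The shift in this table applies the same reduced SE to the QALY difference.

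**6. Why the bias is given in SD units.** A ratio needs a true QALY effect, which the protocol does not give. At d = 0.235 with the unadjusted SE, suppose the QALY effect is half the pain effect (0.1175 SD). The overstatement is then 1 + 0.044/0.1175 = 1.37 to 1 + 0.102/0.1175 = 1.87. If the two effects are equal, it is 1 + 0.044/0.235 = 1.19 to 1 + 0.102/0.235 = 1.43. In every case above the shift is below one standard error of the QALY difference.

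**The case against.** The strongest defence is that this is a scope choice declared in advance, not hidden selective reporting. Cost-effectiveness is not among the aims in Objectives {10}, and evaluating cost only after benefit is shown contradicts nothing else in the document. That argues for modest weight. It does not make 52-week pain a sound test of whether costs and QALYs are worth reporting.

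Some stronger readings are tempting, and the documents do not support them:

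- *Nothing is reported if pain is inconclusive.* EQ-5D-5L is a secondary outcome tested by ANCOVA with no condition, so the quality-of-life effect is still available. Only its combination with cost is lost.
- *Only flattering cost-effectiveness results appear.* Programme costs count, so an analysis run after a positive pain result can still be unfavourable.
- *Every programme target enters EQ-5D-5L directly.* Sleep and weight are not among the five dimensions, and pain is.
- *The QALY gain is nearly doubled.* That needs a small true pain effect, a high correlation, a QALY effect half as large as the pain effect, and no gain from ANCOVA. At the design effect the overstatement under the same half-effect assumption is 4–8% unadjusted and about 1–3% with ANCOVA.
- *All 228 participants will supply complete data.* The plan itself assumes 15% dropout.

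The article also need not specify how uncertainty in the economic result is computed; that can stand in an analysis plan.

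**Conclusion.** The point holds as a cheap improvement to a secondary analysis. The condition is explicit, appears twice, is undefined, and rests on an endpoint and time frame other than those of the analysis it controls. The main cost is withholding: at the design effect a chance of roughly 1 in 25 (ANCOVA) to 1 in 10 (unadjusted) that the joint result is never produced, rising to more than half if the true pain effect is about half the design value. Selection bias in the QALY difference is real but secondary, and small at the design effect. The sizes rest on reading *effective* as two-sided p<0.05, on 97 per arm, and on the assumed true effects and correlations. The mismatch between condition and analysis does not depend on them.

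**What to change.** In both Outcomes {16} and Plans for assessment and collection of outcomes {25a}, delete the condition and state:

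> The within-trial cost-utility analysis will be done and reported for all randomised participants whatever the WOMAC pain result. Incremental costs and incremental QALYs will be given with their uncertainty.

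Defining *effective* alone would remove the ambiguity but not the withholding.

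Make the change before pain results are known. Trial status gives the last visit as expected on 12 May 2026. Interim analyses {28b} allows the statistician and research assistant access to interim results, so the amendment should be dated and should say whether any pain comparison between arms had been seen.

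The cost is some analyst time if pain turns out inconclusive. No new data collection is needed, and the primary analysis and sample size are unaffected.

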### Harms {17}

There are no anticipated or potential harms to the participants.

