
Who provided: PCPs will be responsible to confirm the diagnosis of knee OA, identify any relevant comorbidities and optimize their control, review current use of pain medications and to refer eligible patients to the RAMP-OA program. The RAMP-Knee OA will be led by a full-time registered nurse (RN) trained by the research team. He or she will be responsible to deliver the core treatments, provide ongoing lifestyle counselling, prioritize participants’ needs, set and agree on goals, and generate strategies to meet the goals. A part-time physiotherapist and dietitian will be consulted on the design and progress of individuals’ weight management plan.

When and How: Patients will be recruited by PCPs in their usual clinic appointments, which are mostly scheduled every 4 months. Eligible patients assigned to the intervention group will be referred to RAMP-Knee OA clinic operated by RN, which will be a face-to-face consultation scheduled every 4 months following patients’ usual clinic appointments. A total of 4 sessions will be provided for each enrolled participant over one year. The first session will last for 40 minutes and serve as an introduction session; the RN will go through individuals’ biopsychosocial risk parameters, identify their needs, provide core treatment recommendations, set goals, and formulate strategies according to patients’ understanding and preferences. The second and the third sessions, each will last for 20 minutes, will provide an opportunity to review compliance with core recommendations, clarify uncertainties, provide ongoing counselling support, and monitor disease progress. The fourth session, which will also last for 40 minutes, will serve as a wrap-up session in which participants will learn about their progress over one year and reinforce life-long lifestyle modifications for healthy joint.

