The RN will provide updates to the PCPs on the progress of their referred patients via electronic reminders in the Clinical Management System (CMS) after each assessment session—or upon request by the PCPs. The reports will detail any strategies and actions agreed with the patients, and their progress to date. The RN will refer the patients back if they require a medication review, e.g., if patients develop side-effects after the use of pain-killers, or if they have any other medical condition that affects participation in the trial or an escalation of care. If the situation is urgent, the RN will discuss with PA on arranging an urgent medical consultation. On the other hand, if the situation is routine, the nurse will make correspondence to the electronic message on the CMS and advise the patient to report this to their PCPs during their usual clinic appointments.

Physiotherapist and dietitian will offer structured training to our RN on weight management. They will also provide on-going support and guidance on the design of individuals’ weight management plan.

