## Control group (usual care)

Patients allocated to the usual care arm will continue receiving their “usual care” at the GOPCs without any additional intervention. “Usual care” typically refers to the established and commonly provided treatments, interventions, and practices that patients would receive in routine clinical practice for their particular condition or disease. In the context of GOPCs in Hong Kong, the follow-up period for all chronic diseases, including knee OA, is typically every 4 months. Each consultation during these visits has an average duration of 3–5 minutes. Within the time constraints of these consultations, physicians will address all chronic diseases, including knee OA, whether it is the main concern or a comorbid condition. Physicians may provide brief healthcare advice, prescribe chronic medications and analgesics if necessary, and refer patients to physiotherapy if indicated. The management approach for knee OA and other chronic diseases will be solely at the discretion of the attending physicians.

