### Criteria for discontinuing or modifying allocated intervention/comparator {15b}

According to the human research ethics approval, participants may withdraw from the study at any time. Participants are informed that the Principal Investigator may terminate the study and their participation at any time if they are deemed unsuitable for participation. Such termination will not affect their usual care received. A “stopping rule” will be applied to participants who underwent knee surgery or experienced severe knee pain during the study period [40]. For any emergencies during the study, participants were encouraged to go to the Accident and Emergency department for timely care. A&E visits are documented as adverse events of the study.

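### The Harms section rules out any potential harm, against the plan's own stopping and adverse-event text, and no equal enquiry about non-urgent events in both arms is stated

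*Protocol article*

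**What the plan says.** The Harms section (item 17) is one sentence: "There are no anticipated or potential harms to the participants".

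The section on criteria for discontinuing or modifying the intervention (item 15b) says: "A “stopping rule” will be applied to participants who underwent knee surgery or experienced severe knee pain during the study period". The rule is not limited to one arm. For emergencies, "participants were encouraged to go to the Accident and Emergency department for timely care", and "A&E visits are documented as adverse events of the study".

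The intervention description has the RAMP nurse refer patients back to their physician "if patients develop side-effects after the use of pain-killers, or if they have any other medical condition that affects participation in the trial" or that calls for escalated care, with an urgent medical consultation if needed. This route belongs to the RAMP arm. On contact, "A total of 4 sessions will be provided for each enrolled participant over one year", whereas controls "will continue receiving their “usual care” at the GOPCs without any additional intervention".

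Both arms are assessed at weeks 16, 32 and 52 (Participant timeline), by research assistants blinded to allocation (item 24b). Emergency visits and hospital stays are self-reported at 0 and 12 months for the preceding three months and supplemented from Hospital Authority records. The Outcomes section describes this under cost-effectiveness.

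**The concern.** The Harms section makes a categorical statement, so the allowance for what a condensed article leaves out does not cover it. The programme consists of strengthening, stretching and aerobic exercise, plus weight management where BMI is 23 or more. It is given to adults aged 45 or over with knee pain of at least 4 out of 10. Taken at its word, the Harms section leaves nothing to look for, although the same article defines stopping events, names an adverse-event category and assigns safety monitoring to the coordinating centre.

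The statistical issue is ascertainment. The one named category is emergency attendance. Lesser events have no stated place, and the only described setting in which someone would hear of them and act is the nurse session, which one arm has and the other lacks. If such events entered the record, they would be counted under different conditions in the two arms. If they did not, the trial would have little to say about them. The Discussion presents the trial as a reference for managing knee OA in primary care, where readers will expect some account of safety.

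**Working it through.** The article gives no harms figure to reproduce. The only plan figure used below is 114 per arm. The exact t-test calculation for a standardised difference of 0.469, 90% power and two-sided alpha 0.05 gives 96.5, so 97 per arm. Then 97/0.85 = 114.1, which agrees with the stated 114 apart from rounding up.

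**Step 1: consistency of the text.**
- Item 17: no harm anticipated or potential.
- Item 15b: severe knee pain and knee surgery foreseen as stopping events; A&E visits foreseen and classed as adverse events. An absolute denial and a definition of adverse events cannot both describe the same plan.
- Intervention description: analgesic side-effects and conditions needing escalation foreseen. This is a weaker tension, because the text does not attribute them to the programme.

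**Step 2: what is measured alike in both arms.**
- WOMAC pain at weeks 16, 32 and 52.
- Analgesic use, by diary and by recall of the past 14 days at each assessment.
- Public A&E and hospital use, from Hospital Authority records.
- Self-reported service use. The 12-month report covers 3 of the 12 follow-up months, or 25%; the baseline report covers time before the trial.

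**Step 3: what has no stated equal enquiry.** Falls, strains and brief flares between visits that do not lead to A&E or hospital. Attendance at private providers is also outside the public records, and the comparator section allows private treatment.

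**Step 4: the difference in contact.** RAMP sessions last 40 + 20 + 20 + 40 = 120 minutes; the control arm has 0 additional minutes.

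**Step 5: why nurse-reported events must stay out of the comparison.** This is conditional: no section says that what the nurse hears becomes a trial adverse event. Suppose it did, with the same true event rate p in both arms and capture shares c(R) and c(C) in RAMP and control. Recorded rates are p·c(R) and p·c(C). With n = 114 per arm, the chance of a significant but false difference, by the two-sided 5% normal test of two proportions, is

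Φ{ [ |p1 − p2|·√n − 1.96·√(2·p̄(1 − p̄)) ] / √( p1(1 − p1) + p2(1 − p2) ) }

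where p1 and p2 are the recorded rates and p̄ is their mean.

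| True rate (assumed) | Capture RAMP / control (assumed) | Recorded rates | False significance |
|---|---|---|---|
| 20% | 80% / 40% | 16% / 8% | 46% |
| 20% | 60% / 40% | 12% / 8% | 17% |
| 10% | 80% / 40% | 8% / 4% | 24% |
| 10% | 60% / 40% | 6% / 4% | 10% |

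Row 1: (0.08 × 10.677 − 1.96 × 0.4596)/0.4561 = −0.10, and Φ(−0.10) = 0.46. The nominal level is 5%. The true rates and capture shares are assumptions, so the table shows direction and rough scale and does not estimate what this trial will record.

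**The case against.** The strongest reply is that this is a wording problem. The article condenses an ethics-approved protocol in which adverse-event definitions and forms would normally sit, and the coordinating centre is charged with safety monitoring. Severe knee pain is part of the natural course of a disease with entry pain of at least 4 out of 10, analgesic side-effects belong to usual care in both arms, and no safety objective is stated. Most of this stands. It means the stopping rule alone does not show that the programme is expected to cause harm, and that a fuller procedure may exist. It does not rescue the Harms sentence, which asserts that harms are absent.

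A reader might infer two stronger things. The first is that A&E visits are the only events that will be recorded. The article says they are adverse events; it does not say nothing else is. The second is that harms cannot be compared fairly at all. Public A&E and hospital attendances can be retrieved for both arms, and WOMAC pain and analgesic use are measured alike, so the gap is confined to non-urgent events. Nor is unequal counting demonstrated: data collection is assigned to the blinded assistants, and what the nurse hears is routed to clinical care.

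It would also be wrong to cite the upper 95% limit after zero events in 114 patients (1 − 0.05^(1/114) = 2.6%) as a sign of a defect. It reflects arm size and would be the same however well harms were collected.

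**Conclusion.** The point holds in a limited form. The Harms statement contradicts item 15b and sits badly with the escalation text in the intervention description, so these sections must be reconciled. Separately, the article secures no equal enquiry in both arms about non-urgent events, while one arm has four extra sessions in which they could come to light. A between-arm comparison of such events would be open to detection bias, and the likely direction is more events noticed under RAMP. The document does not allow its size to be estimated.

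The second part rests on the article as printed: if the full protocol contains an arm-neutral adverse-event enquiry, only the contradiction remains. The primary WOMAC analysis is not affected.

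**What to change.** 1. Replace the Harms sentence with the foreseeable events (pain flare, fall, exercise-related injury, A&E or hospital attendance) and reconcile it with item 15b and the intervention description. This concerns recording and reporting only. The content of the stopping rule is for the investigators.
2. Have the blinded research assistants ask the same fixed adverse-event question in both arms at every week-16, 32 or 52 assessment still to come.
3. Tabulate nurse-reported events separately and keep them out of the between-arm comparison.
4. Extract public A&E and hospital attendances over the full 52 weeks for all 228 participants from Hospital Authority records and report them by arm, whether or not the cost-effectiveness analysis is triggered. At present that analysis depends on a reduction in WOMAC pain.

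Two limits should be stated with the results. First, coverage of the question will be partial. Recruitment ran from 1 April 2024 to 12 May 2025. Someone enrolled on the first day reached week 52 around 31 March 2025; for someone enrolled on the last day, week 16 falls around 1 September 2025 and week 32 around 22 December 2025. The last visit is expected on 12 May 2026. If few or no visits remain, items 1, 3 and 4 can still be done. Second, private care is not in the public records.

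The cost is a minor ethics amendment, one question at visits already scheduled, and a record extraction somewhat larger than the one described for cost-effectiveness.
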